### The intervention

The ACF2, commissioned and funded by YEF, will test specialist multi-agency and multi-disciplinary teams (referred to as multi-agency hereafter) located in neighbourhoods to support children and young people aged 10–20 years (and their families or carers) who are at risk of, or experiencing, violence or criminal exploitation outside the home [18]. Figure 1 presents the a priori high-level programme theory of change and Additional file 1 provides the detailed a priori programme theory of change (developed by YEF).

**Fig. 1 Fig1:**
[figure not shown]
A priori high-level programme theory of change

The programme will be delivered across five sites, and at site level the local programme will be led by the local authority. The multi-agency teams will consist of statutory organisations, voluntary, community, faith, and social enterprise (VCFSE) organisations, the police, probation, mental health professionals (for children and young adults), and education. The composition of each site’s multi-agency team will be based on local context, needs, and strengths and assets; thus, there will be some variation across sites (Additional file 2 presents a high-level summary of site-level programmes). Multi-agency teams will work within trusted community settings (e.g. community centres, libraries, schools), and key workers will build direct relationships with children and young people (and their families/carers where appropriate) to coordinate and advocate for support. The programme will combine work currently implemented at ‘targeted early help’, ‘child in need’, and ‘child protection’ and ‘in care’, and transitional safeguarding support for young adults aged 18–20 [16]. Support will be person/family-centred and strengths-based and thus the nature, type, and dosage of support will be determined by the individual needs of each child/young person/family unit. The targeted support for children and young people (and their families/carers) may be complemented by interventions delivered in the neighbourhood that aim to address the underlying causes of and contextual factors relating to extra-familial harm.

## Methods

### Setting and site selection processes

The programme will be delivered in ten neighbourhoods across five local authority areas in England and Wales (two neighbourhoods per site) to enable exploration of if and how different contexts influence implementation. These are Cardiff (East Cardiff neighbourhood [St Mellons, Llanrumney, and Trowbridge] and North Cardiff neighbourhood [Llanishen, Pentwyn, Pontprennau, and Llanedeyrn East]), East Sussex (Castle and Devonshire wards), Newham (East Ham and Plaistow), Swansea (East area and Penderry), and Swindon (one neighbourhood consisting of Park North, Park South, and Walcot East; and one neighbourhood consisting of Pinehurst and Penhill).

The independent evaluation team (led by authors [name]) and programme sites were selected using an application process commissioned by the YEF [18], who invited local authorities in England and Wales to apply for the Agency Collaboration Fund: A Supportive Home grant round. The funding aims to test specialist multi-agency and multi-disciplinary teams located in two neighbourhoods to support children and young people aged 10–20, and their families/carers who are vulnerable to—or experiencing—violence or criminal exploitation outside the home. The grant round funded up to five local authorities to put into action recommendations from the Independent Review of Children’s Social Care. Amongst other criteria (listed in full in [18]), eligible sites were those with high rates of youth violence and/or offending by children and young people across the local authority and within the selected neighbourhoods; potential for future programme scale up; and a good state of readiness to deliver the multi-agency programme. Applicants were shortlisted and invited to an interview panel that included YEF and members of the independent evaluation team. Five sites were selected from the shortlisted applicants based on evaluation criteria which included the extent to which the planned programme of work aligned with the YEF specification [18] and outcome framework [19]; evidence that the programme differs from ‘business-as-usual’; the feasibility of the site reaching 200 children and young people; alignment of neighbourhood sites with relevant geographies to enable area-level evaluation; and feasibility of availability and access to relevant local partnership data.

Successful applicants were supported through the preparation (~9 months) and implementation (11 months) phase with a YEF-appointed co-design partner. In the preparation phase, site-level partnerships prepared for programme implementation through the development of a local systems map; site-level theory of change, and partnership delivery model and associated policies. Sites progressed to programme implementation in April 2024.

### Sampling, participant recruitment, and eligibility criteria

#### Sample size

For the feasibility and pilot of the impact evaluation phase of this study, pre- and post-outcome measures will be collected from 1000 young people who receive key worker support (~200 per site). This sample size target was a pragmatic decision, agreed a priori between the evaluation team and the funder (YEF), on the basis that this would provide a good indication of intervention reach and of the ability of sites to recruit a sufficient number of participants to evaluate impact in a full trial. Our target number of 10 neighbourhoods exceeds the 8 identified by Hemming and colleagues in their overview of external pilot studies [20], and our total sample size exceeds the 30 participants per site recommended by Lancaster et al. [21] and the 35 per group recommended by Teare et al. for estimating the uncertain critical parameters (including standard deviation for continuous outcomes, and consent, event, and attrition rates for categorical outcomes) [22]. For the feasibility of the implementation phase of this study, interviews will be completed with 100–125 stakeholders (20–25 per site), 75 children and young people (15 per site), and 75 parents/carers (15 per site). Participants will be selected purposefully to ensure diversity across and within sites. For stakeholders, the number of participants will be guided by the delivery context of each multi-agency team and saturation. Children and young people and parents/carers will be purposefully sampled (in collaboration with gatekeepers who provide a safeguarding role) to ensure diversity in relation to socio-demographics and guided by saturation.

#### Recruitment and consent

As the delivery of the multi-agency programme will be closely embedded with the delivery of statutory services, in many cases, children and young people will have a legal right to receive the statutory elements of provision. Therefore, participants will consent to the programme and the evaluation as separate entities. Before children and young people can take part in the study, the correct consent procedure must be followed. Parent/carers of children aged 10–15 years may ‘opt-out’ their child (i.e. inform the key worker if they do not want the child to take part). For interviews with children aged 10–15 years, parent/carers have the opportunity to ‘opt-in’ their child (i.e. inform the key worker if they do want the child to take part). All children and young people will have the opportunity to assent/consent to their own participation.

#### Children and young people with key worker support (pre- and post-outcome measures)

Children and young people (and parents/carers as appropriate) will be provided with an introduction to the study and an invitation to take part via their key worker. This will include a verbal description of the study, provision of relevant (e.g. age and developmentally appropriate) information sheets, and an opportunity to ask questions and consider their participation. For children and young people, filling in the questionnaire implies their assent/consent. During this consent process, children and young people and their parents/carers must also consent for their data to be deposited in the YEF data archive.^1^ To be eligible for the study, children and young people need to be receiving key worker support, aged 10–20 years, at risk of or experiencing extra-familial harm, and have the capacity to provide informed consent/assent. Further, the key worker must deem that there are no current (or previous) safeguarding risks that would be impacted by the child or young person’s inclusion in the study that cannot be addressed through minor amendments to study design.

#### Parents/carers and children and young people (interviews)

Key workers will identify potential children and young people, and parent/carers to invite to participate in an interview. They will provide them with an information sheet and the participant will be able to ask their key worker any questions and will also be provided with contact details for the research team. The researcher will explain the study verbally again at the start of each interview; copies of participant information sheets will be available for participants, and they will have the opportunity to ask questions.

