### Data collection and outcomes

#### Assessment of routine programme monitoring data

We will work with delivery sites to set up routine monitoring/assessment processes to monitor all stages of delivery including programme uptake (e.g. number/profile of children and young people/families/carers referred/engaged/supported), dosage (e.g. number/type of interventions/referral pathways), distinction (from business as usual), and attrition, across activity strands. With participant consent, data will be linked via a pseudo-anonymised code to individual-level pre-post outcome measurements.

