**Additional criteria**				
** (Adverse) effects of programme participation**	From preliminary analysis of outcome data and qualitative data	No evidence of substantial negative effects of participation		Evidence of substantial negative effects of participation
** Acceptability of programme activities**	From analysis of qualitative data	Target groups report programme activities and interventions are acceptable and/or could be feasibly improved	Target groups report programme activities/interventions are unacceptable and cannot identify how they could be improved. Sites develop plan to increase acceptability	Target groups report programme activities/interventions are unacceptable and cannot identify how they could be improved. Sites cannot identify a plan to increase acceptability
** Acceptability of evaluation methods**	From analysis of qualitative data	Target groups report evaluation methods are acceptable and/or could be feasibly improved	Target groups report evaluation methods are unacceptable and cannot identify how they could be improved. Evaluator/sites develop a plan to increase acceptability	Target groups report evaluation methods are unacceptable and cannot identify how they could be improved. Evaluator/sites cannot identify a plan to increase acceptability
** Programme implementation**	From analysis of theories of change and system maps, and interviews with providers	Programme is coherent: meets criteria for multi-agency approach and is distinct from business as usual	Programme is not coherent: does not meet criteria for multi-agency approach and is not distinct from business as usual. Sites identify plan to improve coherence	Programme is not coherent: does not meet criteria for multi-agency approach and is not distinct from business as usual. Sites cannot develop a plan to improve coherence

^a^RIP—Research in Practice, the programme co-design partner

^b^E.g. weekly

^c^E.g. 6-monthly, annually

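### Key workers, who deliver the programme, identify the families to be interviewed, so the two acceptability rows of Table 3 and the qualitative part of the adverse-effects row rest partly on a sample nominated by deliverers

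*Protocol article*

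**What the plan says.** The section on interviews with parents/carers and young people sets the route into the sample: "Key workers will identify potential children and young people, and parent/carers to invite to participate in an interview". The key worker also hands over the information sheet and answers questions.

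The section on the intervention describes these same staff as deliverers: "key workers will build direct relationships with children and young people (and their families/carers where appropriate) to coordinate and advocate for support".

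The Sample size section plans 15 young people and 15 parents/carers per site. It says they will be "purposefully sampled (in collaboration with gatekeepers who provide a safeguarding role) to ensure diversity in relation to socio-demographics and guided by saturation". A general sentence just before asks for diversity across and within sites but names no dimension.

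The qualitative data collection section invites families at 12 weeks. If young people turn out to complete or leave before then, the team will aim to reach them sooner, for example at 6 weeks. It gives no other way of identifying them.

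In Table 3, under the additional criteria, both acceptability rows take qualitative data as their indicator. For programme activities, the top rating reads: "Target groups report programme activities and interventions are acceptable and/or could be feasibly improved". The row for evaluation methods is worded in parallel. The adverse-effects row draws on preliminary outcome data and on qualitative data.

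**The concern.** The staff whose work is under assessment put forward the people who will assess it. With 15 young people interviewed out of about 200 supported per site, they have wide room to choose. A key worker who wants cooperative interviewees, or who has simply lost touch with some families, will tend to name those who are engaged. A sample that is diverse in age, gender, ethnicity and socio-economic status can still consist entirely of engaged families.

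This matters because the interviews inform a decision. An acceptability row falls below *fully met* only when target groups find the activities or methods unacceptable and cannot say how they could be improved. The families most likely to report that are also the ones least likely to be nominated. The limitations in the Discussion do not mention this.

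**Working it through.** **1. The plan's own figures.** Five sites × 15 = 75 young people, and the same for parents/carers. Five sites × 200 = 1000 supported young people. The totals reproduce. The interviewed share is 15/200 = 75/1000 = 7.5%.

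**2. Which rows of Table 3 depend on these interviews.**
- Acceptability of programme activities: qualitative data, on what target groups report.
- Acceptability of evaluation methods: the same.
- (Adverse) effects: outcome data planned from about 1000 young people, plus qualitative data. The qualitative data also include 100–125 stakeholders. Only part of this row is exposed.

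**3. Whether another section supplies a different route.** The Sample size section brings in gatekeepers but asks only for socio-demographic diversity in these groups. The provision for early leavers changes when they are approached, not who identifies them. Neither adds engagement or drop-out as a criterion.

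**4. Illustration of size.** The document gives no rate of dissatisfaction and no nomination pattern, so both are assumptions. Let *p* be the share of supported young people who find the programme unacceptable, and *w* their chance of being nominated relative to others. The share among interviewees is

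q = wp / (wp + 1 − p).

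The chance of none among a site's 15 is (1 − q)^15, and among all 75 it is (1 − q)^75. This assumes the same *p* and *w* at every site and independent nominations.

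| p | w | q | expected of 15 | expected of 75 | none of 15 | none of 75 |
|---|---|---|---|---|---|---|
| 10% | 1 | 0.100 | 1.5 | 7.5 | 21% | 0.04% |
| 10% | 0.5 | 0.053 | 0.8 | 3.9 | 44% | 1.7% |
| 10% | 0.1 | 0.011 | 0.2 | 0.8 | 85% | 44% |
| 20% | 1 | 0.200 | 3.0 | 15.0 | 3.5% | <0.01% |
| 20% | 0.5 | 0.111 | 1.7 | 8.3 | 17% | 0.01% |
| 20% | 0.25 | 0.059 | 0.9 | 4.4 | 40% | 1.1% |
| 20% | 0.1 | 0.024 | 0.4 | 1.8 | 69% | 16% |
| 30% | 1 | 0.300 | 4.5 | 22.5 | 0.5% | <0.01% |
| 30% | 0.5 | 0.176 | 2.6 | 13.2 | 5% | <0.01% |
| 30% | 0.2 | 0.079 | 1.2 | 5.9 | 29% | 0.2% |
| 30% | 0.1 | 0.041 | 0.6 | 3.1 | 53% | 4% |

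Worked line: p = 0.20, w = 0.5 gives q = 0.10/(0.10 + 0.80) = 0.111; 0.889^15 = 0.17.

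**5. Reading the table.** Moderate selection can thin or remove critical voices at one site. It rarely removes them from all 75; that needs strong selection, and a low *p* makes it more likely. The 75 parent/carer interviews are not in the table. They come by the same route, but they are not independent of the young people's interviews where both come from one family.

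**The case against.** A reader might infer that the adverse-effects row as a whole is judged on a hand-picked sample. The document does not support that: the row also uses outcome data planned from about 1000 young people, and qualitative data from stakeholders. Those outcome data are not a complete safeguard, because the questionnaires are completed at the delivery site with the key worker's help, and 60% follow-up completion already counts as *fully met*. They are nonetheless not nominated by key workers in the way the interviewees are.

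A reader might also infer that early leavers are left out. They are not: the plan aims to reach them sooner. What stands is that nobody other than the key worker is named to identify them.

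A third inference would be that deliverer nomination produces a *fully met* rating. This cannot be shown. The acceptability rows have no count or proportion, the top rating already allows for feasible improvement, and qualitative work needs critical themes to surface, not to appear in proportion. Under 30% dissatisfied and one-fifth nomination, the chance that none of the 75 young people is dissatisfied is about 0.2%. Progression is also a discussion of all criteria with the funder.

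The remaining counter-arguments have some force. Purposive sampling is normal in qualitative research. The wording about collaboration with gatekeepers implies that the evaluators have some part in selection. A service-experience questionnaire is planned for the whole questionnaire sample, although it is not a stated indicator for either acceptability row. Access through key workers has a real safeguarding reason, but that supports a veto more than it supports nomination. Finally, the article condenses a fuller study plan that is not shown and may add criteria. Against that, the article does not leave the identification step open; it assigns it to key workers.

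**Conclusion.** The point holds in limited form. Two progression rows on acceptability, and the qualitative part of a third on adverse effects, rest partly on interviewees nominated by the staff who deliver the programme. For these groups the only stated diversity criterion is socio-demographic. Disengaged or dissatisfied families may be under-represented, and the plan does not acknowledge this.

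The size cannot be derived from the document. With assumed dissatisfaction of 20% and nomination at one-half to one-quarter of the usual rate, the chance of hearing no dissatisfied young person at a given site goes from 3.5% to between 17% and 40%. Over all five sites it stays at about 1% or less. These are illustrations for single sites; Table 3 does not say that the acceptability rows are rated by site, and they carry no numeric cut-off. The change is worth making because it is cheap and bears on a progression criterion.

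**What to change.** In the Sample size section and the section on interviews with families:
- Add engagement level and drop-out status to the purposive sampling criteria, alongside socio-demographics.
- Once the monitoring system is in place, have the evaluators specify for each site whom to invite, using the pseudonymised codes. The plan already intends to "monitor all stages of delivery including programme uptake", together with dosage and attrition.
- Let the key worker pass on the invitation and withhold it only on safeguarding grounds. Log each withholding and report the number by site.

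Report acceptability by engagement group. In the Discussion, state any remaining gatekeeper selection as a limitation.

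The cost is a change of wording, a sampling list per site and a short log. Interview set-up becomes slightly slower. The list also depends on the completeness of site monitoring data, which is still to be set up with the sites; Table 3 treats up to 35% missing baseline monitoring data as *fully met*. Contact still runs through the key worker, so the safeguarding role is kept.

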#### Stakeholders (interviews/focus groups)

Stakeholders will be purposefully selected to ensure diversity and capture the whole complex system surrounding each multi-agency team. Stakeholders will include delivery leads, multi-agency team members, and wider partners. Stakeholders must be over 18 years, able to give informed consent, and involved in the delivery of the multi-agency programme. Stakeholders will be approached by a gatekeeper (site-level programme lead) who will explain the study and ask if they are happy to have their contact details shared with the researchers. The researcher will provide them with a participant information sheet and give them the opportunity to ask questions before taking consent and arranging a suitable time and date for the interview. The study's purpose will be explained again verbally at the beginning of each interview and participants will be given the opportunity to ask questions.

### Data collection and outcomes

#### Assessment of routine programme monitoring data

We will work with delivery sites to set up routine monitoring/assessment processes to monitor all stages of delivery including programme uptake (e.g. number/profile of children and young people/families/carers referred/engaged/supported), dosage (e.g. number/type of interventions/referral pathways), distinction (from business as usual), and attrition, across activity strands. With participant consent, data will be linked via a pseudo-anonymised code to individual-level pre-post outcome measurements.

#### Review of programme documentation and refinement of programme description

We will collate and review programme documentation to add context to the study. This may include delivery plans (including theories of change), programme promotion material, steering group minutes, and YEF programme monitoring forms. The TIDieR-PHP (Template for Intervention Description and Replication for Population Health Programmes) reporting guideline will be completed with sites [23].

#### Qualitative data collection: interviews/focus groups

Interviews (virtual or via telephone^2^) will be undertaken with children and young people, parents/carers, and stakeholders to examine views and experiences of programme implementation and outcomes/impacts, co-production and feedback loops, and as relevant evaluation design and outcome measurements. General topic guide templates will be developed to ensure consistent coverage across participants, and adapted, as appropriate, for each participant group to reflect their varying roles within the programme. Questions will be age and developmentally appropriate and culturally sensitive.^3^ Public involvement and engagement (PPIE) consultations were carried out with young people engaged in youth services at site level to ensure the interview topic guide was acceptable and comprehensible to participants. Interviews will be semi-structured and approximately 30–60 min in duration. We will engage with practitioners at delivery months 3–4 (programme steering group, key workers, and members of the multi-agency team) and delivery months 10–11 (programme steering group, key workers, members of the multi-agency team, and wider community members) to enable timely feedback/adaptations prior to feasibility/pilot study completion. Engagement with children and young people, and parents/carers will be ongoing throughout the study period, with participants invited to interview at 12 weeks following formal programme engagement.^4^ If it becomes apparent that children and young people complete or drop out of the programme before the 12-week follow-up point, we will aim to engage with them at an earlier stage (e.g. 6 weeks).

